### Pharmacokinetics

**Drug dose:** there were five cohorts , or five dose groups: 150 mg, 230mg, 300mg, 350mg and 400 mg.

**Time of blood sample collection:** According to the guiding principles of human pharmacokinetic research, and combined with the characteristics of long-acting ropivacaine injection, the preliminarily planned time of blood sample collection from healthy subjects was shown in **Table 2** The blood collection point of the subsequent cohort can be adjusted according to the actual drug time curve obtained from the low-dose cohort of healthy subjects.

**Table 2 Blood sample collection time for pharmacokinetic studies**

| No | Blood collection time point          | Time window |
|----|--------------------------------------|-------------|
| 1  | Within 15 min before administration  | /           |
| 2  | 0.5h after the end of administration | ±2 min      |
| 3  | 1 h                                  | ±2 min      |
| 4  | 1.5 h                                | ±2 min      |
| 5  | 2 h                                  | ±2 min      |
| 6  | 4 h                                  | ±5 min      |
| 7  | 6 h                                  | ±5 min      |
| 8  | 8 h                                  | ±5 min      |
| 9  | 10 h                                 | ±5 min      |
| 10 | 12 h                                 | ±5 min      |
| 11 | 14 h                                 | ±5 min      |
| 12 | 21h                                  | ±5 min      |
| 13 | 24 h                                 | ±5 min      |
| 14 | 27 h                                 | ±5 min      |
| 15 | 30 h                                 | ±5 min      |
| 16 | 33h                                  | ±5 min      |
| 17 | 36 h                                 | ±5 min      |
| 18 | 48h                                  | ±5 min      |
| 19 | 72 h                                 | ±5 min      |

## Biological sample processing procedures

**Identification of biological samples:** Before blood sample collection, the blood vessel collection and plasma sample cryopreservation tubes should be numbered uniformly, and special labels should be pasted to identify the words: The first item in the label is the hospital project number; Number of the plan of conduct; The third line ##### is the subject number, XX is the blood collection site number; The fourth behavior sample type: whole blood is used for vacuum vascular collection, plasma is used for cryopreservation tube, A is plasma detection, B is backup plasma; \*\*min/h represents the blood collection point of the subject.

**PK sample collection:** 4mL of venous whole blood was taken into a blood collection tube containing EDTA-K2 anticoagulant. Immediately, the test tube was gently reversed 4-5 times after blood collection to ensure that the blood and anticoagulant were fully mixed, and to avoid prolonged contact between the blood sample and rubber plug. Centrifugation was completed within 1h after collection (4°C, 2000g, 10min), the upper plasma was divided into two cryopreservation tubes (specification :2mL)(test plasma A and backup plasma B), and the plasma samples were transferred to the ultra-low temperature refrigerator (-60 ~-90) within 2h(calculated from the blood sample collection) for biological analysis.

**PK biological sample transfer:** After sample collection of the whole test, the plasma will be transported by cold chain company in a sample transport box at -60°C~-90°C to the testing company for plasma concentration determination.. Temperature during transportation is monitored in real time and biological samples cannot be reversed..

**Determination of drug concentration in plasma:** The concentration of ropivacaine free base in human plasma was determined by LC-MS/MS method. This method strictly complies with relevant requirements for sufficient confirmation, including specificity; matrix effect; standard curve, linear range, lower limit of quantification; intra-batch and inter-batch variation; residual and dilution effects; recovery test; standard, internal standard placement stability test, mother liquid stability test, whole blood placement stability test, freeze-thaw stability test, repeated injection stability test, post-preparation stability test, room temperature placement stability, long-term stability, etc.

**Estimation and evaluation of pharmacokinetic parameters:** Pharmacokinetic curves and average pharmacokinetic curves of all subjects were drawn according to the drug concentration-time data measured in the trial, and pharmacokinetic parameters (mean and standard deviation) were calculated. The main pharmacokinetic parameters included: Tmax, Cmax, AUC0-t, AUC0-∞, Vd, Kel, T1/2, CL etc.

## Pharmacodynamics methods:

**Experimental design, (1) Analgesic range measurement (Experiment 1) :** After the single point of administration, pain points were determined in two directions (when the VAS value of the test point (n) 1cm away from the point of administration was  $\geq 4$ , The measurement can be terminated at (n+1) time point) at 15min, 30min, 45min $\pm$ 3min, 1h, 1.5h, 2h, 3h, 4h, 5h, 6h, 7h, 8h, 9h, 10h, 11h, 12h  $\pm$ 5min, respectively. The distance between pain point and drug administration point (R1, R2) was measured and recorded, and the analgesic range diameter D = (R1 + R2).

**(2) Analgesic maintenance time, onset time and acupuncture pain intensity were measured (Test 2):** the intensity of acupuncture pain was measured before and after 15min, 1h, 4h, 8h, 10h, 12h, 14h, 18h, 21h, 24h, 27h, 30h, 33h, 36h, 48h, 72h;

**Baseline pain measurement:** Before drug administration, visual analogue scale (VAS) was used to measure the pain pressure baseline value (g) of VAS=4,5,6 in the pain test area, repeated for 3 times, and average value was taken respectively, namely the baseline value;

**Acupuncture pain intensity measurement:** a baseline value of VAS=4 was applied to the blank area to remind subjects of the sensation; In the pain test area, the baseline VAS=4 pressure was applied to the area, and the subjects were asked to compare the feeling with the blank area, and the feeling was "weaker", "similar", "stronger"?

When it was "weaker", baseline pressure at VAS= 5,6 was successively given and the inquiry process was repeated. When VAS=6 pressure was applied, subjects felt weaker and did not continue to increase the pressure. When it was "similar", record the maximum pressure value applied at this time; When it was stronger, the maximum pressure of the previous application was recorded and the onset time of analgesia maintenance time and the intensity of acupuncture pain were counted.

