### **Pharmacodynamics index evaluation**

#### **Analgesic onset time:**

**Evaluation of analgesic onset time:** analgesic onset time was recorded as the time when the threshold of measured pain sensation was greater than the threshold of baseline pain sensation of the subject (i.e., baseline

VAS=4 average acupuncture pressure) when the pain sensation was measured after drug administration.

**Pain threshold:** the minimum stimulus intensity when the human body feels pain. Pain threshold usually refers to a stimulus intensity that can cause pain sensation in human body, which is generally divided into pain sensation threshold and pain tolerance threshold (the maximum stimulus intensity that human body can tolerate) .

**Duration of analgesia:** Effective analgesia refers to the pain threshold greater than the baseline pain threshold during pain measurement. Theoretically, the duration of analgesia is the difference between the effective start time and the effective end time of analgesia. However, in the actual operation of this study, real-time dynamic monitoring could not be achieved, so the duration of analgesia in this study was divided into minimum duration of analgesia and maximum duration of analgesia. The true value of analgesic duration was between the minimum duration and the maximum duration.

Minimum duration of analgesia = last time from measurement to effective analgesia - first time from measurement to effective analgesia

Maximum duration of analgesia = (last measured to effective analgesia +1) measurement time - first measured to effective analgesia time

**Table 3: Acupuncture pain intensity: The intensity of acupuncture pain in this study was divided into 3 levels as described in the table below:**

|              |                                                                                                                          |
|--------------|--------------------------------------------------------------------------------------------------------------------------|
| Three Grade  | Pain threshold was measured $\geq$ baseline VAS=6 acupuncture pressure                                                   |
| Second Grade | Baseline VAS=6 acupuncture pressure > threshold of pain sensation $\geq$ baseline VAS=5 acupuncture pressure             |
| First Grade  | Baseline VAS=5 acupuncture pressure value > threshold of pain sensation $\geq$ baseline VAS=4 acupuncture pressure value |

Analgesic range of injection site (Study 1);

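### The Test 2 pressure ladder stores partial analgesia as the baseline pressure, so Table 3's First Grade mixes no change with some effect and can never count as effective analgesia

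*Protocol*

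**What the plan says.** Under *Pharmacodynamics methods*, the baseline step is to "measure the pain pressure baseline value (g) of VAS=4,5,6 in the pain test area, repeated for 3 times", with the repeats averaged. Call the three resulting pressures P4, P5 and P6. At each later time, "a baseline value of VAS=4 was applied to the blank area to remind subjects of the sensation". P4 is then pressed on the test area and the subject says whether it feels weaker, similar or stronger.

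- *Weaker* leads to P5 and then P6. Escalation stops at P6.
- *Similar* records the pressure just applied.
- For *stronger*: "When it was stronger, the maximum pressure of the previous application was recorded".

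Under *Pharmacodynamics index evaluation*, onset is the time when "the threshold of measured pain sensation was greater than the threshold of baseline pain sensation of the subject", and baseline there means the average VAS=4 pressure. For duration: "Effective analgesia refers to the pain threshold greater than the baseline pain threshold during pain measurement". The Protocol adds that the true duration lies between its minimum and maximum formulas.

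Table 3 has three grades. The lowest runs from the baseline VAS=4 pressure, inclusive, up to the VAS=5 pressure: "Baseline VAS=5 acupuncture pressure value > threshold of pain sensation". There is no grade for no analgesia.

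**The concern.** Each rule is workable alone. Storing the previous step is a legitimate lower bound for a threshold. Combined with a strict greater-than criterion and a lowest grade that includes equality, it loses information. A reading that shows a raised threshold is stored as if nothing had changed.

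Onset, duration and intensity in Test 2 all come from this one stored value. *Secondary purpose* uses them to settle the spacing of doses. *Pharmacodynamics analysis* feeds them into the Kaplan-Meier summaries and the mixed model. This is a data-capture rule. The Protocol asks only for the pressure to be recorded, and if that is all that is stored, no later analysis can separate no effect from partial effect.

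**Working it through.** The Protocol gives no figure for this point to reproduce, so the check is to enumerate the ladder and then apply the Protocol's own definitions.

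**Step 1. All reply sequences**

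| Replies on the test area | Recorded | Table 3 grade | Greater than P4? |
|---|---|---|---|
| stronger at P4 | unclear | unclear | unclear |
| similar at P4 | P4 | First | no |
| weaker at P4, stronger at P5 | P4 | First | no |
| weaker at P4, similar at P5 | P5 | Second | yes |
| weaker at P4 and P5, stronger at P6 | P5 | Second | yes |
| weaker at P4 and P5, similar at P6 | P6 | Third | yes |
| weaker at all three | P6 (implied) | Third | yes |

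The second and third rows share one stored value and one grade, although the third row reports reduced sensation at P4. Only P4, P5 or P6 can be stored, so First Grade always means exactly P4. No First Grade reading can be effective analgesia.

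**Step 2. Direction.** Readings that count as effective are a subset of readings felt as weaker at P4. Recorded onset therefore cannot be earlier, and recorded minimum and maximum durations cannot be longer, than if the third row counted. If no partial reading falls on the grid, the shift is zero.

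**Step 3. Illustration on the grid.** The times under *Observation indicators* are 15 min, then 1, 4, 8, 10, 12, 14, 21, 24, 27, 30, 33, 36, 48 and 72 h. (*Pharmacodynamics methods* also lists 18 h, which does not alter this example.) Assumed profile: partial at 1 h, P5 or more from 4 to 30 h, partial at 33 and 36 h, none at 48 h.

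- As written: onset 4 h; minimum 30 − 4 = 26 h; maximum 33 − 4 = 29 h.
- Partial readings counted: onset 1 h; minimum 36 − 1 = 35 h; maximum 48 − 1 = 47 h. The two brackets do not overlap.
- Partial at 1 h and 33 h only: onset 1 h; minimum 33 − 1 = 32 h; maximum 36 − 1 = 35 h.

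Take one partial reading at each end, recorded onset between 1 and 12 h, and recorded end no later than 36 h. Onset is then 0.75 h (1 − 0.25) to 4 h (8 − 4) late. Minimum duration is 2.75 h (0.75 + 2) to 16 h (4 + 12) short. Maximum duration is 2.75 h (0.75 + 2) to 28 h (4 + 24) short.

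**Step 4. Noise cost of counting partial readings.** Assume no analgesia, independent normal reply noise with SD *s* of 0.3 to 0.5 VAS units, steps one unit apart, and a just-noticeable difference *j* of 0.25 to 0.5. None of these inputs is in the Protocol.

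- P(weaker at P4) = Φ(−j/s)
- P(recorded above P4) = Φ(−j/s) × Φ((j − 1)/s)

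| s | j | weaker at P4 | recorded above P4 |
|---|---|---|---|
| 0.3 | 0.25 | 0.202 | 0.202 × 0.0062 = 0.001 |
| 0.5 | 0.25 | 0.309 | 0.309 × 0.067 = 0.021 |
| 0.3 | 0.5 | 0.048 | 0.048 × 0.048 = 0.002 |
| 0.5 | 0.5 | 0.159 | 0.159 × 0.159 = 0.025 |

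About 5 to 31% of readings with no analgesia would be felt as weaker at P4, against 0.1 to 2.5% recorded above P4 now. Over 15 independent times, 1 − (1 − p)^15 gives at least one false effective reading with probability 52 to 99.6%, against 2 to 32% under the present rule.

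**The case against.** The strongest reply is that requiring a full step of gain is a sensible conservative convention. Step 4 supports it: counting every reply of weaker at P4 as effective would let noise create early onsets and long durations, because duration runs from first to last effective reading with no continuity requirement. This stands as an argument about the threshold. It does not rescue the text, which defines effective analgesia as anything above baseline rather than as reaching P5, and it does not justify discarding the distinction at capture.

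Several stronger readings are tempting but unsupported:

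- **Onset is always late and duration always short.** This needs a partial reading on the grid. Otherwise nothing shifts.
- **Every untreated reading is First Grade.** This holds only for replies of similar at P4.
- **A reply of stronger at P4 is lost.** P4 has just been pressed on the blank area, so that press might be meant as the previous application. The rule is unclear, and loss is not established.
- **The cap at P6 and the linear model are faults.** The Protocol states the cap openly and Table 3's top grade is open upward. No bias from the linear model has been shown.

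The instruction to repeat the inquiry could also mean pressing P5 and P6 on the blank area. The partial sequence would still be stored as P4.

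**Conclusion.** The point holds as a contradiction between the recording rule, the definition of effective analgesia and Table 3. Partial analgesia is stored as baseline. First Grade pools it with no change, and no First Grade reading can be effective. Where partial readings occur on the grid, recorded onset is later or equal, both recorded durations are shorter or equal, and the claim that true duration lies between the minimum and maximum can fail. This takes the subjects' replies at face value.

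The size cannot be derived from the Protocol. The hours and percentages above illustrate stated assumptions and are not estimates for this trial. The affected measures are secondary indicators; safety and pharmacokinetics are untouched. The reason to act is that the lost distinction cannot be recovered if only the pressure is kept.

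**What to change.** 1. Record the reply (weaker, similar or stronger) at each pressure step in the CRF.
2. In Table 3, add Grade 0 for similar or stronger at the VAS=4 pressure, and limit Grade 1 to weaker at VAS=4 followed by stronger at VAS=5. Grades 2 and 3 stay as they are.
3. State what is recorded for a reply of stronger at VAS=4.
4. Align *Pharmacodynamics index evaluation*. Either keep effective analgesia at Grade 2 or higher (the VAS=5 pressure or above) and describe onset and duration as conservative, or also report both with Grade 1 or higher as a sensitivity analysis.
5. Reword the sentence on true duration to match.

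Grade 1 should not be the sole definition of effective analgesia, because it is sensitive to reply noise (about 5 to 31% false readings under the assumptions in Step 4). The cost is CRF coding, Table 3 and some wording. The pressures applied to subjects do not change.

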### **Observation indicators:**

#### **The main indicators include:**

- (1) the safety and tolerability experiment observation indexes: including clinical symptoms and signs laboratory tests local skin irritation at the injection site reactions assessment of adverse events (including systemic adverse reactions, and the injection site appearance at the injection site pain, tenderness at the injection site erythema or redness at the injection site induration , swelling At the injection site itching, etc.);
- (2) The observation indexes of single point optimal subcutaneous dose exploration test included skin irritation score at injection site and average diameter of analgesic range (Test 1);
- (3) Pharmacokinetic test detection: pharmacokinetic parameters of ropivacaine concentration in plasma.

**Secondary indicators:** Pharmacodynamic test observation indicators: The analgesic effect duration, acupuncture pain intensity and analgesic onset time of the two drugs in experimental group and positive control group were observed and compared. Duration of analgesia; Analgesic onset time; Acupuncture pain intensity; Analgesic range of injection site (study 1); The straight-line distance between two adjacent dosing points on the same circumference.

**Pharmacokinetics:** Experiment 2 was conducted to investigate pharmacokinetics. Blood concentration-time data and pharmacokinetic parameters of single dose were investigated. Combined with the characteristics of ropivacaine injection, and referring to the clinical pharmacokinetic test report of experimental drug in beagle dogs, the blood sample collection time of healthy subjects was preliminarily determined as follows: Within 15min before administration and 0.5h, 1h, 1.5h, 2h, 4h, 6h, 8h, 10h, 12h, 14h, 21h, 24h, 27h, 30h, 33h, 36h, 48h and 72h after administration. The concentration of ropivacaine in human plasma was determined by LC-MS/MS. The pharmacokinetic parameters were calculated by drawing the pharmacokinetic curves and average pharmacokinetic curves of each subject according to the concentration time data of each subject measured in the experiment.

#### **Pharmacodynamics:**

- (1) Maintenance time of analgesia, onset time and intensity of acupuncture pain were measured: the intensity of acupuncture pain was measured before and after administration at 15min, 1h, 4h, 8h, 10h, 12h, 14h, 21h, 24h, 27h, 30h, 33h, 36h, 48h and 72h.
- (2) Analgesic range measurement: 15min, 30min, 45min, 1h, 1.5h, 2h, 3h, 4h, 5h, 6h, 7h, 8h, 9h, 10h, 11h, and 12h after single point administration, analgesic range was measured in two directions (study 1).

### **Pharmacodynamics index evaluation**

#### **Analgesic onset time:**

**Evaluation of analgesic onset time:** analgesic onset time was recorded as the time when the threshold of measured pain sensation was greater than the threshold of baseline pain sensation of the subject (i.e., baseline

VAS=4 average acupuncture pressure) when the pain sensation was measured after drug administration.

**Pain threshold:** the minimum stimulus intensity when the human body feels pain. Pain threshold usually refers to a stimulus intensity that can cause pain sensation in human body, which is generally divided into pain sensation threshold and pain tolerance threshold (the maximum stimulus intensity that human body can tolerate) .

**Duration of analgesia:** Effective analgesia refers to the pain threshold greater than the baseline pain threshold during pain measurement. Theoretically, the duration of analgesia is the difference between the effective start time and the effective end time of analgesia. However, in the actual operation of this study, real-time dynamic monitoring could not be achieved, so the duration of analgesia in this study was divided into minimum duration of analgesia and maximum duration of analgesia. The true value of analgesic duration was between the minimum duration and the maximum duration.

Minimum duration of analgesia = last time from measurement to effective analgesia - first time from measurement to effective analgesia

Maximum duration of analgesia = (last measured to effective analgesia +1) measurement time - first measured to effective analgesia time

**Table 3: Acupuncture pain intensity: The intensity of acupuncture pain in this study was divided into 3 levels as described in the table below:**

|              |                                                                                                                          |
|--------------|--------------------------------------------------------------------------------------------------------------------------|
| Three Grade  | Pain threshold was measured $\geq$ baseline VAS=6 acupuncture pressure                                                   |
| Second Grade | Baseline VAS=6 acupuncture pressure > threshold of pain sensation $\geq$ baseline VAS=5 acupuncture pressure             |
| First Grade  | Baseline VAS=5 acupuncture pressure value > threshold of pain sensation $\geq$ baseline VAS=4 acupuncture pressure value |

Analgesic range of injection site (Study 1);

The straight-line distance between two adjacent dosing points on the same circumference.

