### **Pharmacodynamics analysis**

Pharmacodynamics indexes were described by mean, standard deviation, maximum, minimum and median, and compared with the basic value in screening period. Paired T test was used to compare the differences before and after treatment in groups.

The groups were compared using a least square mean of the difference from baseline (with baseline as a covariable) and a 95% confidence interval.

The mixed effect model was used to analyze the change of acupuncture pain intensity at different time points after

administration compared with that before administration. The model took the change value of pain intensity at different time points in different administration areas compared with baseline as the dependent variable, and the pain intensity before administration as the covariable. Group (experimental group, control group), administration area/blank area, visit site, and interaction between group and visit site were fixed effects and individual factors were considered.

According to the model, the mean value of change in pain intensity at different time points of administration from baseline and its 95% confidence interval were calculated, as well as the mean value of difference between the experimental group and the control group and its 95% confidence interval.

Similar methods were used to analyze the range of analgesia.

Kaplan-meier method was used to statistically analyze the onset time and maintenance time of analgesia, and the median, Q1, Q3 and 95% confidence interval of the onset time and maintenance time of analgesia were calculated.

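### The stated maximum duration of analgesia allows for the unseen end of the effect but not its unseen start, so the true duration can exceed it

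*Protocol*

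**What the plan says.** Under Pharmacodynamics index evaluation (Protocol), the paragraph on duration of analgesia starts from the target quantity: "Theoretically, the duration of analgesia is the difference between the effective start time and the effective end time of analgesia". It explains that "real-time dynamic monitoring could not be achieved", and so replaces the single value by two limits. The lower limit is the time of the last effective reading less the time of the first effective one. The upper limit is worded as follows: "Maximum duration of analgesia = (last measured to effective analgesia +1) measurement time - first measured to effective analgesia time".

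The paragraph also gives a guarantee: "The true value of analgesic duration was between the minimum duration and the maximum duration".

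Under Pharmacodynamics analysis, "Kaplan-meier method was used to statistically analyze the onset time and maintenance time of analgesia". That section does not say whether the minimum, the maximum or some other value is entered as the duration. Observation indicators lists duration and onset of analgesia among the secondary indicators.

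**The concern.** Start and end of analgesia are both observed only at scheduled readings, so both are uncertain. The maximum allows for one of the two. In both formulas the start is fixed at the first effective reading, which is the latest time the effect can have begun, not the earliest. An upper limit built on the latest possible start is not an upper limit, and the containment sentence is then wrong as written.

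At stake is the interval reported for each subject, which the protocol presents as certain to hold the true value. The error grows with the gap before first detection, so it need not be equal between preparations. The preclinical summary describes a slower effect for the long-acting product in rabbits, against almost complete block at about 5 min for ropivacaine mesylate. If that carried over to humans, the shortfall would be larger for the test drug.

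**Working it through.** The protocol gives no numerical example of the bracket, so there is no figure to reproduce. The check is interval arithmetic on its own definitions.

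**Inputs.** Duration is end minus start. Reading times after administration are given as "15min, 1h, 4h, 8h, 10h, 12h, 14h, 21h, 24h, 27h, 30h, 33h, 36h, 48h and 72h" (Observation indicators, Pharmacodynamics; Table 10 note 19 gives the same list). Pharmacodynamics methods adds an 18 h reading: "15min, 1h, 4h, 8h, 10h, 12h, 14h, 18h, 21h, 24h". The two lists agree up to 14 h. Time 0 is administration. Analgesia is taken as one continuous episode.

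**Limits.** Let t(first) and t(last) be the first and last effective readings.

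- Start lies after t(first−1) and no later than t(first).
- End lies no earlier than t(last) and before t(last+1).
- Shortest duration: t(last) − t(first). This equals the protocol's minimum.
- Longest duration: just under t(last+1) − t(first−1).
- Protocol's maximum: t(last+1) − t(first).
- Shortfall: t(first) − t(first−1), the gap before first detection.

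**Size of the shortfall.**

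| First effective reading | Reading before it | Shortfall (upper bound) |
|---|---|---|
| 0.25 h | 0 | 0.25 h |
| 1 h | 0.25 h | 0.75 h |
| 4 h | 1 h | 3 h |
| 8 h | 4 h | 4 h |

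**Examples.**

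| First | Last | Next | Minimum | Stated maximum | Correct maximum |
|---|---|---|---|---|---|
| 1 h | 12 h | 14 h | 12 − 1 = 11 | 14 − 1 = 13 | 14 − 0.25 = 13.75 |
| 4 h | 12 h | 14 h | 12 − 4 = 8 | 14 − 4 = 10 | 14 − 1 = 13 |
| 8 h | 12 h | 14 h | 12 − 8 = 4 | 14 − 8 = 6 | 14 − 4 = 10 |
| 4 h | 36 h | 48 h | 36 − 4 = 32 | 48 − 4 = 44 | 48 − 1 = 47 |

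**How often the maximum is exceeded.** This needs an assumption. Let g1 be the gap before first detection and g2 the gap after the last effective reading, with start and end uniform within their gaps. The chance that the truth exceeds the stated maximum is g1/(2·g2) if g1 ≤ g2, otherwise 1 − g2/(2·g1). For a last effective reading from 8 to 48 h, g2 runs from 2 h (readings 8 to 10 h) to 24 h (48 to 72 h):

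- First detected at 15 min: 0.25/48 = 0.5% to 0.25/4 = 6%.
- At 1 h: 0.75/48 = 2% to 0.75/4 = 19%.
- At 4 h: 3/48 = 6% to 1 − 2/6 = 67%.
- At 8 h: 4/48 = 8% to 1 − 2/8 = 75%.

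**Effect of the correction on a duration estimate.** In a simulation with assumed log-normal durations (medians 8, 12 and 24 h, log-SD 0.3) and onset uniform between 0.05 and 1 h, on both reading lists, the mean error was −1.7 to −2.8 h for the minimum, +1.0 to +2.3 h for the stated maximum and +1.6 to +3.0 h for the corrected maximum. The corrected bracket always contained the truth, and the minimum was never violated.

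**Two edge cases.** 72 h is the last reading, so a subject still effective then has no following reading and the maximum is undefined. For a last effective reading at 14 h, the following reading is 18 h on one list and 21 h on the other, which changes the maximum by 3 h.

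**The case against.** The strongest reply is that little turns on this. Duration is a secondary indicator; escalation and termination rest on safety; there are only 3 control subjects, all in cohort A. Only the upper limit can fail. If analgesia is first detected at 15 min, the shortfall is at most 0.25 h, no more than the ±15 min measurement window in Table 10 note 19. A maximum that is too low understates how long a slow-onset product may last, so it does not favour the test drug, and the minimum, which would support a claim of long action, is sound. All of this stands and limits the weight of the point. It does not rescue the formula or the guarantee attached to it.

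A reader might infer more than the protocol supports:

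- *That the bracket misses the truth in general.* It need not contain the truth. Any miss is at the upper end only and smaller than the gap before first detection.
- *That the Kaplan-Meier estimate is biased by this omission.* The protocol does not say which duration is entered, and a statistical analysis plan may. In the simulation above the stated maximum already overestimates on average, and the corrected maximum does so more. Bias in the estimate comes from treating interval-censored times as exact, which is a separate matter.
- *That a stray late effective reading often sets the end time.* The definition requires no unbroken run, but the protocol gives no error rate for such replies, and each reading is compared with the blank area. No size can be put on this.

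Kaplan-Meier can accommodate right-censoring at 72 h, so that gap concerns the written definition of the maximum, not the chosen method.

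**Conclusion.** The formula and the containment sentence are wrong as written. The stated maximum can be too low by up to 0.25, 0.75, 3 or 4 h for first detection at 15 min, 1 h, 4 h or 8 h. These figures follow from the protocol's own reading times and need only the assumption of one continuous episode of analgesia. The stated minimum is correct.

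The frequency of exceedance is not known. The range of 0.5% to 75% above rests on uniform start and end times within gaps, and on where first and last detection fall; the protocol gives no human onset or offset figures. The shortfall is small if effect is detected by 1 h and material if it is first seen at 4 h or 8 h. This is a moderate correction to a secondary indicator and does not affect the main objectives.

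**What to change.** In the duration paragraph, define the maximum as the measurement time after the last effective reading minus the measurement time before the first effective reading, using 0 if the first post-dose reading is already effective. State that a subject still effective at 72 h is right-censored, with no finite maximum. The two lists of reading times must be reconciled on 18 h, since the following reading depends on it.

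Under Pharmacodynamics analysis, or in the statistical analysis plan, state which duration is analysed. Either treat onset and offset as interval-censored, or show Kaplan-Meier results for both the minimum and the corrected maximum. Correcting the formula repairs the bracket; it does not by itself remove bias from the duration estimate, and the corrected maximum should not be used alone as the estimate.

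The cost is a change of wording and a few lines of code, with no new data. The downside is wider reported intervals.
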